### Outcomes

Figure 1 provides a summary of standardised outcome measures to be completed during the study using the SPIRIT template.

**Fig. 1 Fig1:**
[figure not shown]
Summary of enrolment, intervention and assessment procedures based on the SPIRIT figure [30]


#### Secondary outcome measures

##### Theory of Mind (ToM)

The strange stories task [47] will be used as the primary measure of change in ToM. Parallel versions of the task will be administered to children at baseline 1, baseline 2, post-intervention and follow-up. The strange stories task contains 12 social stories in which there is a discrepancy in characters’ perspectives or beliefs and children must explain the discrepancy with reference to characters’ thoughts and feelings. Responses are scored on a 3-point Likert scale (0 = no reference to thoughts and feelings, 1 = reference to thoughts or feelings, 2 = reference to thoughts and feelings). A single total ToM score is generated by summing items (range = 0 to 24). Three control stories from the strange stories task that are comparable in length and difficulty, but contain no reference to thoughts or feelings of characters, will also be administered to obtain a measure of general story comprehension (range = 0 to 6). The strange stories task was selected as empirical studies have found that children with GGE and TLE have significant impairments on this task [6, 7]. An additional (secondary) measure of change in ToM will be obtained with the Theory of Mind Inventory (TOMI) [48], which will be completed by parents at the same 4 time points. The TOMI is a 42-item parent-report questionnaire that assesses ToM in children aged 3 to 17 years old. Parents rate how accurate statements are for their child on a 5-point Likert scale (1 = definitely not true to 5 = definitely true), and scores are summed to generate a total raw score (range = 42 to 220), which is converted into a percentage total score (range = 0 to 100). The TOMI is being included as it has been found to be sensitive to change following interventions in other clinical populations [48].

##### Social competence

The social competence subscale of the Self-Perception Profile (SPP) [49] will be used as the primary measure of change in social competence. The SPP will be completed weekly by both children and parents from baseline 1 to follow-up. The SPP consists of parallel child (6 items) and parent (3 items) forms, which assess a child’s social skills, peer acceptance and popularity among peers. For each item, the rater chooses one of two statements that best describes the child and then rates how true that statement was over the past week (really true or sort of true). Each item is scored from 1 to 4, with a total score calculated by averaging all items (range = 1 to 4). A higher score indicates better social competence. The SPP has been selected as it is considered a valid and reliable self-rated measure of social competence in children, is sensitive to change following interventions and includes a parent-rated version that parallels the child scale, which is considered critical for adequately assessing social outcomes [50]. Additional (secondary) measures of social competence will be obtained with standardised, parent-report questionnaires: the Strength and Difficulties Questionnaire (SDQ, total problems subscale; total raw score will be used for interpretation) [51] and the Child Behavior Checklist (CBCL, social competence subscale; *t* scores will be used for interpretation) [52]. These will be completed at baseline 1, baseline 2, post-intervention and follow-up. They are being included as (i) impairments on these measures were related to impairments in ToM in prior studies of children with epilepsy [6, 7] and (ii) these scales are widely employed and validated questionnaires, which may be useful for future trials and clinical care. Ratings that differ between parents and children will be followed up in debriefing interviews to determine possible causes of discrepancy. Contradictory findings on different measures will be used to revise research methods and select outcome measures for an ongoing trial.

#### Baseline cognitive measures

Figure 1 outlines cognitive tests to be completed by children assessing IQ, EF and general language skills. These will be completed at baseline 1 only. The Wechsler Abbreviated Scale of Intelligence for Children–Second edition (WASI-II; Vocabulary, Similarities, Block design, Matrix Reasoning) [53] will be used to obtain a brief estimate of general intellectual abilities. The Peabody Picture Vocabulary Test–Fourth Edition (PPVT–4) [54] will be used as a measure of receptive vocabulary (general language skills). The Automated Working Memory Assessment (AWMA) Backward Digit Recall subtest [55] will be used to assess verbal working memory. The Delis-Kaplan Executive Functions System (D-KEFS) Colour-Word Reading test [56] will be used as a measure of behavioural inhibition. These are being included as knowledge of children’s baseline cognitive skills may provide useful information about individual participants ability to engage with or benefit from activities, which may be useful for drawing conclusions about the suitability of tasks using the case series approach [35].

#### Demographic and clinical variables

Semi-structured interviews with parents at baseline 1 will be used to obtain information about demographic and epilepsy factors (i.e. age of seizure onset, seizure frequency, current medications, surgical status), the child’s current social and emotional functioning and any psychosocial treatment they have received in the past. Treating neurologists will complete the Global Assessment of Severity of Epilepsy (GASE) [57] at baseline 1 to obtain an overall measure of epilepsy severity. The GASE is a validated, single-item questionnaire that asks clinicians to rate severity of epilepsy from 1 to 7, with a higher score indicating more severe epilepsy.

### Participant timeline

Figure 2 provides an overview of procedures for recruitment, delivery of the intervention and assessments.

**Fig. 2 Fig2:**
[figure not shown]
Study design diagram: procedures for recruitment and delivery of the intervention and assessments

#### Procedure for recruitment

Children with epilepsy will be recruited from an existing research database at participating hospitals. All children invited for the current study participated in a previous cross-sectional study conducted between 2015 and 2017, and parents/guardians have consented to be re-contacted for future studies. In the previous study, children completed tasks at a single time point assessing ToM and relevant cognitive skills (e.g. IQ, EF). Parents completed questionnaires assessing social competence of their child. Parents and children received a brief rationale for why we were studying social cognition in epilepsy, but no discussion or explanation was provided for an intervention nor was this available at the time that the cross-sectional study was conducted. Participants identified as eligible will be mailed out PICFs, which contain an expression of interest form for parents to sign and return to investigators. As we are only recruiting 10 to 12 children, the first eligible children in the database will be re-contacted. Participants who express interest will be contacted by telephone and a screening interview will be conducted to confirm eligibility. Participants who do not return the expression of interest form within 2 weeks of it being mailed out will be contacted by telephone to explain the study and determine whether they are interested and eligible. If the parent and child are eligible and interested, parents will be provided with details of the study (i.e. dates and locations of sessions) and a time will be arranged for the initial assessment session.

#### Procedure for intervention delivery and assessments

Children will participate in 4 small group workshops held over 4 consecutive weeks at the Psychology Clinic at The University of Sydney. Each workshop will last for approximately 2 to 3 h and will be divided into 2 to 3 sessions (20 to 50-min each), each separated by a 10- to 15-min break. The final 15- to 30-min of each session will be a review with parents and children.

Children will complete 4 one-to-one assessments with an investigator at baseline 1 (4 weeks before the intervention begins), baseline 2 (1 day before the intervention begins), post-intervention (last day of intervention) and follow-up (4 weeks after the intervention). During assessments, children will complete a behavioural task assessing ToM and parents/guardians will complete questionnaires that assess ToM and social competence of their child. A brief weekly measure of social competence will be completed by both parents and children from baseline 1 to follow-up. Assessments with children will be conducted individually, face to face, at The University of Sydney Psychology Clinic or participants homes. Parent questionnaires and weekly measures will be completed online.

Following completion of the intervention, parents and children will attend face-to-face debriefing interviews to discuss the child’s participation and provide feedback. Parents will complete two online questionnaires assessing treatment acceptability and barriers and facilitators to attending the programme. Children will complete a single questionnaire assessing treatment acceptability that parallels the questionnaire completed by parents. These questionnaires will be completed before the debriefing interview to minimise bias in responding based on clinician feedback.

### Data collection and data management

The intervention and assessments will be conducted by psychologists and neuropsychologists who are trained and experienced in administering the tasks included in the assessment battery and intervention sessions. Thus, no additional training will be required for any of the investigators. To promote participant retention and completion of follow-up, home visits will be offered for assessments, as this has been found to almost double retention rates in pilot studies [58]. Home visits will not be offered for intervention sessions, as being exposed to treatment in a different learning environment may add a source of bias to results. Participants who discontinue or withdraw prior to completion of the study will not be required to complete any further assessments, as per requirements of the governing ethics committee. It is not anticipated that participants could deviate from the study protocol in any way other than discontinuing sessions.

Each participant will have a unique identification (ID) code assigned to them at the start of the study, which will be used to de-identify data and link information collected on paper and in electronic forms. During the study, de-identified data will be stored securely in the original paper and electronic copies in locked filing cabinets and password-protected files, respectively, at The University of Sydney. Codes and consent forms will be stored separately to the files themselves in a separate locked filing cabinet. After completion of the study, all data will be converted to secure electronic files and stored in password-protected files at The University of Sydney. Data will be retained until participants are 25 years of age or for a minimum of 15 years (whichever is later) as per the Australian Code for the Responsible Conduct of Research [59]. Data will only be accessible to study investigators listed on the ethics application. There are no external sponsors or other involved parties that will have access to data.

### Statistical methods

Primary analyses will report results relating to feasibility outcomes, which do not rely on quantitative statistical tests. Secondary analyses will involve data pertaining to children’s performance on tasks of ToM and social competence. Individual participant scores on secondary outcome measures will be plotted graphically and visual analysis will be used to assess change in performance from baseline 1 to follow-up. Visual analysis involves inspecting performance during an intervention and at follow-up and comparing this to a baseline mean (i.e. average of scores at baselines 1 and 2) [60]. Although new quantitative methods have been devised to estimate effect sizes in case studies, the use of these measures has been advised against in pilot studies due to the potential for inaccurate interpretation of results with unpowered samples [61]. Thus, visual analysis along with inspection of simple, descriptive statistics was considered the most appropriate method for the current study. Both primary and secondary analyses will be used to draw a conclusion about whether the study should be expanded into a larger scale trial. Given the small sample size and lack of quantitative statistical tests, we do not anticipate that statistical methods will be required to handle missing data; however, missing data for individual participants will be reported in papers arising from the research with an explanation of why data was not obtained.

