### Overall success of the intervention

The overall success of the intervention and decision to evaluate it in a larger scale trial will be determined with both primary and secondary outcomes. A final decision about the protocol will be made upon completion of the study [32]:Stop (main study not feasible). None of the primary feasibility outcomes are met *and* a negative trend is observed in secondary outcomes *or* other adverse effects are reported.Continue but modify protocol (feasible with modifications). One or more of the primary feasibility outcome measures are not met.Continue without modifications (feasible as is). All of the primary feasibility outcomes are met *and* a positive trend is observed on both secondary outcomes (ToM and social competence).

Trends on secondary outcomes will be determined with visual analysis, as described in the “Statistical methods” section. A negative trend would be indicated by scores that fall below the baseline mean and positive trends by scores that fall above the baseline mean [60]. Scores that are comparable to baseline or fluctuate around the baseline mean would indicate neither a positive nor negative trend. A negative trend for ≥ 50% of participants would be sufficient to stop the main study (decision a). A positive trend on ≥ 50% of participants will be considered sufficient to continue the study, with or without modifications (decisions b or c). Smith [60] provides further details about this method. Participants included in the pilot study will not be included in an ongoing trial that results from this research to reduce the potential for bias in results.

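### The weekly SPP gives about five pre-treatment scores per rater, but the baseline mean that decides its trend uses only two of them

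*Protocol article*

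**What the plan says.** In the Social competence section, the SPP subscale "will be used as the primary measure of change in social competence", and "The SPP will be completed weekly by both children and parents from baseline 1 to follow-up". The section on intervention delivery and assessments repeats the schedule ("A brief weekly measure of social competence will be completed by both parents and children from baseline 1 to follow-up") and dates the two baseline visits: "baseline 1 (4 weeks before the intervention begins), baseline 2 (1 day before the intervention begins".

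The Statistical methods section sets one method for all secondary measures: "Individual participant scores on secondary outcome measures will be plotted graphically and visual analysis will be used to assess change in performance". Change is judged by "comparing this to a baseline mean (i.e. average of scores at baselines 1 and 2". It gives no separate rule for the measure taken weekly.

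The section on overall success builds its classification on that mean: "A negative trend would be indicated by scores that fall below the baseline mean and positive trends by scores that fall above the baseline mean". Scores close to the mean, or moving around it, count as neither. The classification then feeds a threshold: "A negative trend for ≥ 50% of participants would be sufficient to stop the main study (decision a", with a matching 50% threshold on positive trends for continuing. Continuing without modification also requires a positive trend on both ToM and social competence.

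**The concern.** A two-visit baseline suits the strange stories task, TOMI, SDQ and CBCL, which are taken only at the four assessments. It does not suit the SPP, which is collected every week through the baseline period. For that measure the rule bases the reference line on two scores when about five will be available.

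The two-score line carries more error than the collected data require, and each child's later scores are read against it. The parent form has only three items, so single ratings may be noisy. With 10 to 12 children, the 50% threshold is 5 or 6 children, so a few classifications can change what the social competence result contributes to the decision about a larger trial.

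This is not a detail left to a fuller document. The article states the rule and applies it to all secondary measures.

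**Working it through.** The plan has no power, alpha or precision figure to reproduce. Its one relevant figure is the number of scores in the baseline mean, which is 2.

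**Step 1: count the pre-treatment SPP scores.** Take the first workshop as day 0. Baseline 1 is 4 weeks earlier (day -28) and baseline 2 is day -1. Weekly completion gives days -28, -21, -14 and -7, plus day -1 if the SPP is also completed at baseline 2 (assumed). That makes 5 scores. The stated mean uses days -28 and -1, so 3 of 5 (60%) stay out of it.

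**Step 2: standard error of the reference line.** Assume error SD 1 and a week-to-week correlation ρ that decays as ρ to the power of the gap in weeks. Neither figure is in the protocol. With the five scores evenly spaced (weeks 0 to 4):

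- two scores: variance = (1 + ρ⁴)/2
- five scores: variance = (5 + 8ρ + 6ρ² + 4ρ³ + 2ρ⁴)/25

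| ρ | Variance, 2 scores | Variance, 5 scores | SE, 2 scores | SE, 5 scores |
|---|---|---|---|---|
| 0 | 0.5000 | 0.2000 | 0.71 | 0.45 |
| 0.3 | 0.5040 | 0.3226 | 0.71 | 0.57 |
| 0.5 | 0.5312 | 0.4450 | 0.73 | 0.67 |
| 0.7 | 0.6200 | 0.6157 | 0.787 | 0.785 |

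The SE falls by about 37% at ρ = 0, about 20% at 0.3, about 8% at 0.5, and by practically nothing at 0.7. Placing the last score at day -1 instead of day 0 leaves the figures for ρ = 0.3 and 0.5 unchanged to two decimals, and gives 0.791 against 0.789 at 0.7.

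**Step 3: effect on a comparison with later scores.** Only the baseline changes here. Suppose the later performance is summarised by the mean of four weekly follow-up scores, weeks 9 to 12, after four intervention weeks. This summary is an illustration; the plan does not specify it.

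- variance of the four-score mean = (4 + 6ρ + 4ρ² + 2ρ³)/16, which is 0.2500, 0.3884 and 0.5156 at ρ = 0, 0.3 and 0.5
- SD of the difference = √(baseline variance + follow-up variance - 2 × covariance)

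| ρ | 2-score baseline | 5-score baseline |
|---|---|---|
| 0 | √(0.5000 + 0.2500) = 0.87 | √(0.2000 + 0.2500) = 0.67 |
| 0.3 | √(0.5040 + 0.3884 - 2×0.0004) = 0.94 | √(0.3226 + 0.3884 - 2×0.0002) = 0.84 |
| 0.5 | √(0.5312 + 0.5156 - 2×0.0078) = 1.02 | √(0.4450 + 0.5156 - 2×0.0057) = 0.97 |

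Placing the scores on calendar days (-28 to -1, then 28 to 49) moves these by no more than about 0.01: 0.94 to 0.85 at ρ = 0.3 and 1.01 to 0.97 at ρ = 0.5.

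For one later score with independent errors, the SD goes from √(1 + 1/2) = 1.22 to √(1 + 1/5) = 1.10, a fall of about 11%.

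**The case against.** The strongest reply is that this is an exploratory feasibility pilot. The SPP is a secondary outcome, change is judged by eye without tests, and one baseline definition for all measures is simple. The neutral class, for scores that hover around the baseline mean, absorbs some of the error in the reference line. The article also refers to a cited methods source, not available here, for further detail on visual analysis. The precision gain depends on a correlation the protocol does not state. Because the same child is rated each week on fairly stable attributes, that correlation may be substantial. All of this stands. It limits the size of the point, but it does not explain why the reference line should leave out scores that will already be in hand.

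Three stronger readings are tempting, and the document does not support them.

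- A reader might infer that the interim scores are thrown away and that baseline instability would go unseen. Individual scores are to be plotted and change inspected from baseline 1 to follow-up, so the interim SPP scores are on the graph. Only the reference line omits them.
- A reader might set one later score against a two-score baseline (SD 1.22) beside a four-score follow-up mean against a five-score baseline (SD 0.67), and credit the whole drop to the baseline. That changes both ends at once. Of the drop of 0.55, about 0.36 (1.22 to 0.87) comes from averaging the later scores. Nor does the plan say that a single later score decides the trend; it refers to scores in the plural.
- A reader might conclude that a known share of children will be misclassified. The plan sets no numerical boundary between a trend and fluctuation around the mean, so no such rate follows from it.

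**Conclusion.** The point holds as a modest, nearly free improvement to a rule the plan states. For its primary social competence measure, the protocol bases the trend reference line on two of about five available pre-treatment scores per rater. Using all five cuts the standard error of that line by about 37% at best, by about 8% at a weekly correlation of 0.5, and not at all near 0.7.

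This rests on weekly completion as scheduled, on an SPP score at baseline 2, and on an assumed error structure. It does not invalidate the pilot or its feasibility outcomes. It matters because the reference line feeds the rule for stopping or continuing, in a sample where 5 or 6 children reach the threshold.

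**What to change.** Add one sentence to the Statistical methods section: for the SPP, child and parent forms, the baseline mean is the average of all weekly scores completed before the first workshop. Keep the planned visual comparison of both the intervention-phase and the follow-up scores against that mean. Limiting the comparison to the follow-up weeks would drop scores the plan intends to inspect. Keep the two-visit mean for the strange stories task, TOMI, SDQ and CBCL. If the sponsor prefers two scores for the SPP as well, the protocol should say why.

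The change needs no extra data and adds no burden for families. It should be fixed before any scores are examined. There are two small costs: the SPP baseline will be defined differently from that of the other measures, which reports must state, and the gain in precision may be slight if weekly ratings are strongly correlated.

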### Overall success of the intervention

The overall success of the intervention and decision to evaluate it in a larger scale trial will be determined with both primary and secondary outcomes. A final decision about the protocol will be made upon completion of the study [32]:Stop (main study not feasible). None of the primary feasibility outcomes are met *and* a negative trend is observed in secondary outcomes *or* other adverse effects are reported.Continue but modify protocol (feasible with modifications). One or more of the primary feasibility outcome measures are not met.Continue without modifications (feasible as is). All of the primary feasibility outcomes are met *and* a positive trend is observed on both secondary outcomes (ToM and social competence).

Trends on secondary outcomes will be determined with visual analysis, as described in the “Statistical methods” section. A negative trend would be indicated by scores that fall below the baseline mean and positive trends by scores that fall above the baseline mean [60]. Scores that are comparable to baseline or fluctuate around the baseline mean would indicate neither a positive nor negative trend. A negative trend for ≥ 50% of participants would be sufficient to stop the main study (decision a). A positive trend on ≥ 50% of participants will be considered sufficient to continue the study, with or without modifications (decisions b or c). Smith [60] provides further details about this method. Participants included in the pilot study will not be included in an ongoing trial that results from this research to reduce the potential for bias in results.

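### The trend rule runs in one direction for all secondary outcomes, so as written it reverses the SDQ total problems score; any effect on the progression decision depends on whether the SDQ counts

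*Protocol article*

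**What the plan says.** The rule is in the protocol article under Overall success of the intervention: "A negative trend would be indicated by scores that fall below the baseline mean and positive trends by scores that fall above" the baseline mean. There is also a neutral class: "Scores that are comparable to baseline or fluctuate around the baseline mean would indicate neither a positive nor negative trend". A negative trend in at least half of participants is described as enough to stop the main study, and a positive trend in at least half as enough to continue. Continuing without modification requires that "a positive trend is observed on both secondary outcomes (ToM and social competence", together with success on every feasibility outcome.

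Statistical methods says what is classified: "Individual participant scores on secondary outcome measures will be plotted graphically and visual analysis will be used". The reference value comes from "comparing this to a baseline mean (i.e. average of scores at baselines 1 and 2").

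The Social competence section names the SPP as the lead measure of change and gives its direction: "A higher score indicates better social competence". It then adds: "Additional (secondary) measures of social competence will be obtained with standardised, parent-report questionnaires". The first of these is "the Strength and Difficulties Questionnaire (SDQ, total problems subscale; total raw score will be used for interpretation"). The other is the CBCL social competence subscale. No direction is stated for the SDQ, and no reversal or exemption appears.

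**The concern.** The rule speaks of scores lying above or below a mean, not of improvement or worsening, and it covers the secondary outcomes without distinguishing measures. It works only for scales on which higher is better. A raw total of problems runs the other way, so benefit on the SDQ would be recorded as a negative trend and deterioration as a positive one.

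This rule is the only definition of a trend in the article, and trends feed the progression decision. There is no control group and no statistical test that might expose a sign error. The Social competence section also says that conflicting results between measures will inform the methods and the choice of outcomes for a later trial. A child who improved on both SPP and SDQ would appear to have conflicting results purely because of sign, and that could distort the choice.

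**Working it through.** The plan gives no figure to reproduce. The check applies the rule as written to each secondary measure and then follows the result into the decision.

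**Step 1: direction of each measure.**

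| Measure | Role | Direction | Basis | Rule fits? |
|---|---|---|---|---|
| Strange stories (0 to 24) | Lead, Theory of Mind | Higher is better | Scoring described in the article | Yes |
| TOMI | Additional, Theory of Mind | Higher is better | Inferred from what the scale measures | Yes |
| SPP social competence (1 to 4) | Lead, social competence | Higher is better | Stated | Yes |
| CBCL social competence | Additional, social competence | Higher is better | Inferred from subscale name | Yes |
| SDQ total problems, raw total | Additional, social competence | Higher is worse | Inferred from subscale name | No |

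**Step 2: the rule applied to the SDQ, with assumed scores.** Take baselines of 18 and 16.

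- Baseline mean = (18 + 16) / 2 = 17.
- Later scores of 12 and 11 (fewer problems): both are below 17, so the rule gives a negative trend.
- Later scores of 22 and 23 (more problems): both are above 17, so the rule gives a positive trend.

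The scores are only an illustration. The same reversal occurs for any scores clearly away from the baseline mean. Scores close to it fall in the neutral class and are not misread.

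**Step 3: the 50% level as a count.** Planned recruitment is 10 to 12 children. Assuming all are assessed, 0.5 × 10 = 5 and 0.5 × 12 = 6.

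**Step 4: from trend to decision.** The article does not say which measure, or what combination, settles the social competence trend. Three readings are possible.

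- *Only the SPP decides.* The SDQ reversal has no effect on the decision.
- *All social competence measures are weighed together.* A child who improves on every measure shows a positive SPP trend and a negative SDQ trend. The overall classification is then unclear.
- *The SDQ alone decides.* Five of 10 or 6 of 12 children with clearly fewer problems would meet the 50% level for a negative trend. The same number with clearly more problems would meet it for a positive trend.

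**Step 5: with a rule based on benefit.** The SDQ classification flips to the intended one. The classification on strange stories, TOMI and SPP does not change, and the counts stay at 5 of 10 and 6 of 12.

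**The case against.** The strongest reply is that the SDQ is unlikely to drive anything. The SPP is the designated lead measure of social competence and strange stories the lead measure of Theory of Mind, and the rule is right for both. The listed decisions also depend on more than trends. Stopping, as listed, combines failure on all feasibility outcomes with a negative trend, or else rests on adverse effects. Continuing unmodified needs all feasibility outcomes met and a positive Theory of Mind trend as well. Classification is by visual inspection in a study run by registered psychologists and neuropsychologists, who would see what a total problems score means, and the stated aim is improvement. The article also refers to a cited source for details of the method, which is not at hand.

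Much of this stands, and it limits the reach of the point. It does not remove the mismatch. The decision text refers to social competence as an outcome, not to the SPP, and Statistical methods applies visual analysis to the secondary measures without excepting the SDQ. A pre-specified rule should be correct without relying on the reader to correct it. Condensation in an article does not explain the problem either, because both the rule and the measure are stated and they do not fit together.

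A reader might infer more: that benefit on the SDQ would by itself stop the programme, or harm by itself carry it forward unmodified. The article does not support that. The first needs the SDQ to settle the trend, which is not stated, and needs the sentence on the 50% level to override the listed stopping conditions. The second fails because the SDQ cannot supply the feasibility results or the Theory of Mind trend. A reader might also take every score above the mean to count as positive, but the neutral class rules that out.

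**Conclusion.** The point holds for one measure. Followed literally, the trend rule classifies clear improvement on SDQ total problems as negative and clear worsening as positive. The primary measures of change are unaffected.

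This rests on reading the SDQ total problems raw score as higher meaning worse. The article does not state that, but the subscale name leaves no other natural reading. That the SDQ is the only measure affected rests on similar inferences for the TOMI and the CBCL.

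The consequence for the progression decision is conditional: none if only the SPP determines the social competence trend, and up to a full reversal of that trend if the SDQ determines it. The article leaves this open. It is a wording error in a decision rule, worth correcting because the correction is trivial. It is not evidence that the planned decision would come out wrong.

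**What to change.** Under Overall success of the intervention, define a positive trend as change from the baseline mean in the direction of benefit for the measure concerned, and a negative trend as change in the direction of harm. State that for SDQ total problems a score below the baseline mean is positive and one above it is negative. Reversing the SDQ score before plotting would do equally well. Give the direction of the TOMI and the CBCL subscale at the same time, so that none has to be inferred.

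In the same place, say whether the social competence trend is determined by the SPP alone or also by the SDQ.

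The cost is a sentence or two. No data collection, sample size or participant procedure changes. The change should be made before any scores are classified.
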